# Improving Treatment Adherence and Retention of HIV-Positive Women Through Behavioral Change Interventions Aimed at Their Male Partners: Protocol for a Prospective, Controlled Before-and-After Study

**DOI:** 10.2196/19384

**Published:** 2021-01-25

**Keywords:** retention in care, therapeutic adherence and compliance, men's role, acquired immunodeficiency syndrome, AIDS, HIV, behavior, intervention study, health education, community health education, Malawi, mother-to-child transmission, health-related behavior, social ecology

## Abstract

**Background:**

According to the World Health Organization, in 2018, 37.9 million people were living with HIV globally. More than two-thirds were residing in sub-Saharan Africa, where the HIV prevalence in the adult population (aged 15-49 years) was 3.9%. This population included 1.3 million pregnant women, of whom 82% had received antiretroviral therapy (ART) for the prevention of HIV mother-to-child transmission. In these countries, one challenge is an insufficient level of treatment adherence, particularly in HIV-positive pregnant women. Among the causes, the lack of involvement from a male partner is a significant contributor to the problem. This issue has strongly emerged in Malawi, one of the countries with the highest HIV prevalence in the world: 9.2% of its adult population were living with HIV in 2018.

**Objective:**

This study aims to assess 3 interventions that are aimed at improving ART adherence and retention among HIV-positive women through engagement with their male partners in 4 Malawian health care centers.

**Methods:**

The prospective, controlled before-and-after study is conducted in 3 phases (total duration: 24 months): preintervention, intervention, and postintervention analyses. The number of selected clusters (clinical centers) is limited to 4: one for each intervention, plus a cluster where no intervention is performed (control arm). The interventions are as follows: opening the facility on one Saturday per month only for men, defined as a *special day*; testing peer-to-peer counseling among men, *male champions*; and providing a noneconomic incentive to all women who are accompanied by their partners to the facility, *nudge*. The primary outcome of the study is to evaluate the differences in retention in care and adherence to therapeutic protocols among women; the intermediate outcome is the assessment of differences in male involvement. The level of male involvement in the health of their partners (intermediate outcome) will be evaluated through a dedicated questionnaire administered at baseline and in the postintervention phase. Data will be collected at the clinical centers and stored in 2 electronic databases managed using 2 different types of software.

**Results:**

The analysis of data collected in the 4 centers during the preintervention phase is ongoing, as enrollment ended on March 31, 2020. The total number of patients enrolled was 452 (Namandanje: 133; Kapeni: 78; Kapire: 75; and Balaka: 166). Meanwhile, several meetings have been conducted to organize the intervention phase.

**Conclusions:**

The study will identify the best intervention that enhances the involvement of male partners in women’s health, using an approach that considers a broad spectrum of behaviors. An important aspect is the use of educational tools focused on messages, thereby initiating a reflective discussion of stereotypes and false beliefs related to the idea of masculinity present in the Malawian culture.

**International Registered Report Identifier (IRRID):**

DERR1-10.2196/19384

## Introduction

### Background

According to the World Health Organization, in 2018, 37.9 million people were living with HIV globally [1]. The impact of this disease varies considerably across countries and regions. More than two-thirds of people living with HIV are in sub-Saharan Africa (SSA), where HIV prevalence in the adult population is 3.9%. Globally, there were 1.3 million pregnant women living with HIV in 2018 in the region, of whom 82% had received antiretroviral therapy (ART) for the prevention of HIV mother-to-child transmission (PMTCT).

In 2014, the Joint United Nations Programme on HIV/AIDS launched the *90-90-90* program. According to this ambitious plan, 90% of all people living with HIV would know their HIV status, 90% of all HIV people would receive ART, and 90% of all people receiving ART would have viral suppression by 2020 [2]. In most SSA countries, however, the level of adherence is suboptimal, particularly in HIV-positive pregnant women, among whom the adherence rate varies considerably across different settings, both within and across countries, ranging from 35% to 93.5% [3]. There are several barriers to medication adherence that are often linked to different individual factors (sociodemographic and knowledge base), therapy-related factors (complexity of therapy and side effects), social and economic factors, and health care provider and health system–related factors. Stigma and discrimination at the community level and the fear of disclosure of one’s HIV status to their partner are more significant barriers than others [4]. In this scenario, a critical issue is represented by the lack of male partner involvement along the continuum of HIV health care services. This issue represents one of the main reasons for treatment refusal, delayed enrollment, dropout, and low retention of pregnant and breastfeeding women [5-8]. The partner’s lack of involvement, on the contrary, is due to cultural, societal, and gender factors, socioeconomic factors, health service barriers, and policy gaps [9]. Barriers operate at different levels: community (gender issues, role on reproductive health, and stigma), health system (health services tailored to women’s needs and negative attitude of professionals), interpersonal (discordant couples and disclosure issues), and individual (scarce maternal knowledge of child health and fear of stigma) [9]. Therefore, an important challenge is to attain the support of male partners in promoting the health of their female partners. This process includes attending clinics, testing for HIV, and treatment adherence.

Studies have demonstrated that many countries have highly gender-specific and women-centered sexual and reproductive health programs and services [10]. Therefore, men see health-seeking in a maternal setting to be a *woman’s task* and the antenatal clinics as a space for women, and believe that the activities performed are outside their area of responsibility [11]. They perceive that visiting the antenatal clinic would be *unmanly* and they fear stigmatization by other men [11]. The norms related to masculinity discourage men from acceding to health facilities, in particular, to participate in antenatal care (ANC) [12].

Although the importance of male involvement and potential barriers to male involvement are well known, it is not yet clear which public health interventions are effective for attaining male involvement in the health of their female partners, resulting in positive health outcomes for women. There is currently a lack of high-quality studies evaluating the effect of male involvement on women’s health [9]. A 2012 Cochrane review identified only one eligible study pertaining to this issue [13], and a more recent review identified only 12 studies, 6 of which were observational [14]. A limitation of the studies conducted so far on the topic is that they are generally not framed in a theory, model, or framework. Only one of the aforementioned studies designed interventions based on a theoretical model [15]; however, the theory was not considered in the evaluation of results. The use of a theoretical framework allows researchers and health care professionals to be able to design and evaluate interventions by analyzing elements that may favor or decrease the effectiveness of each intervention. This improves the potential for reproducibility of the most effective interventions in different contexts (also known as external validity) [16].

### Design of the Study and Theoretical Framework

In this way, a prospective controlled study is more suitable for the evaluation of promising interventions to improve male involvement and enhance maternal adherence to HIV PMTCT.

For this study, we adopted a framework based on the ecological model [17] adapted by Kaufman et al [18] to health behaviors in HIV prevention. This model considers not only the PMTCT programs that HIV-positive women are engaged with but also the way they live and their relationship with their families and communities. According to the ecological model of health behavior, these are influenced by someone’s living environment, and this influence is articulated at multiple levels. This model, unlike models such as the Health Belief Model [19], does not focus only on individuals and their choices but tries to intervene on all external causes that support or limit positive individual actions [20-22]. In our study, this model aims to overcome the limitations of various adherence support programs that are exclusively based on health education and awareness-raising activities. In many cases, even though HIV-positive women know the importance of adhering to their ART regimens, external elements are preventing them from complying with their prescriptions. These include the attitude of their partner [23], the stigmatization by their community, and the lack of needed resources, both physical and mental.

According to the ecological model, many factors affect male involvement in women’s health care processes at different levels. In this study, we focused on the level presented in Figure 1, namely, individual level, interpersonal and network (eg, family and peers), community, health system (health facility level), and structural level (eg, access to transportation). These critical issues have strongly emerged in Malawi, one of the countries with the highest prevalence of HIV in the world: 9.2% of the adult population (aged 15-49 years) were living with HIV in 2018, and 59.8% of them were women. In 2018, 1 million Malawians were living with HIV, and 13,000 Malawians died from AIDS-related illnesses in the same year [24]. In July 2011, Malawi became the first country to implement the Option B+ approach, which means that all pregnant women living with HIV are offered antiretroviral treatment for life, irrespective of their CD4 count [25]. Between 2011 and 2018, the proportion of female adults with HIV who were diagnosed ranged from 49% to 94% [26]; the proportion of pregnant women with HIV who were virally suppressed jumped from 2% to 48%. The impact of this program has been huge, with a drastic reduction in HIV mother-to-child transmission (MTCT) rates; however, the percentage of male involvement in MTCT and maternal-child health services is still considerably low, ranging from 3.2% to 23% [27].

**Figure 1 figure1:**
[figure not shown]
Effect of multiple integrated component interventions on the social ecological model.

### Aim of the Study

This study aims to evaluate 3 interventions focused on different levels, as described in the ecological model. The primary outcome will be retention and adherence in the care of HIV-positive women, whereas the secondary outcome will be the involvement of male partners in the care of their partners.

## Methods

### Strategy of the Study

The objective of the study is to evaluate 3 different interventions aimed at improving adherence and retention to ART therapy among HIV-positive women through engagement with their life partner. The interventions are (1) testing peer-to-peer counseling and community-level health education sessions delivered by men, *male champions*; (2) opening the facility once a month, only for men, *special day*; and (3) providing incentive to all women accompanied by their partners at the facility, *nudge* or *incentive*.

The different interventions to be implemented and evaluated in the research plan are designed to assess male involvement at the following levels, as depicted in the model represented in Figure 1. The activities that act on the individual and interpersonal or at the social network level common to past studies are transversal to all 3 interventions. At the individual level, both women and their male partners will receive educational content on the importance of retention and adherence to treatments, but also messages that contradict stereotypes and false myths related to masculinity, health, and gender violence. With regard to the interpersonal or social network level, all interventions will include support activities that are aimed at the family (couples counseling).

*Intervention 1* (*Male Champions*) will act at the community level, providing educational interventions that are aimed at territorial communities and religious groups.*Intervention 2* (*Special Day*) will act at the health system level, delivering activities based on health facilities that are aimed at reshaping the clinic as male-friendly.*Intervention 3* (*Nudge*) will also act at the structural level by providing incentives to support the cost of transportation and other costs that reduce a male partner’s ability to access the service.

The study has 3 phases: preintervention (baseline), intervention, and postintervention analyses, as shown in Figure 2.

In the preintervention analysis, the baseline situation of the 3 participating centers will be evaluated. The aim of this phase is to set a starting point to weigh the relative effect of each intervention to be studied. For that purpose, baseline data of each study site will be collected. To evaluate the effect of the interventions, the same indicators will be measured during the pre- and postintervention phases, as described above. The preintervention phase will last 9 months. During this period, data will be collected at each site and included in a database.

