### Interventions

There are several strategies and/or interventions to improve male involvement in the PMTCT process described in the literature. These include psychosocial approaches, verbal encouragement, invitation letters, community education, and sensitization. A review performed by Takah et al [38] showed that psychosocial approaches and complex community interventions are more effective, whereas invitation letters are ineffective. Our review of the literature showed that home visits are one of the most effective single interventions, whereas multicomponent approaches could improve male involvement [14]. After a meticulous analysis of the literature on possible interventions, 3 different types of interventions were selected: (1) community sensitization through male champions; (2) special day for a male-friendly clinic; and (3) incentive to attend the clinical center addressing structural barriers. Each intervention will be performed in a selected center (Table 1).

**Table 1 table1:** The interventions.

Centers	Intervention	Ecological model levels	Activities
Kapire	Male Champions	Individual Interpersonal or social network Community	Individual counseling for men attending DREAM^a^ centers Home care for defaulting male patients Sensitization campaigns in local communities Sensitization campaigns in public spaces (churches, markets, clubs, and bars)
Balaka	Special Day	Individual Interpersonal or social network Health system	Basic health services: HIV testing and counseling Blood pressure measurement Counseling regarding cardiovascular disease Blood glucose measurement and counseling for diabetes Nutritional evaluation and counseling Group educational activities 2 educational sessions using the drama technique
Kapeni	Nudge	Individual Interpersonal or social network Structural	First visit Woman with partner: Food integration is given and an invitation card is delivered. If partners come for the second visit, they receive a second food integration Food integration is not given, but an invitation card is delivered, and if the male partner comes to the second visit, then the family receives a food pack Woman without a partner: Delivery food integration and registration that she has no partner Second visit with partner If the partner accompanies the woman to the center, the personnel will give a food package and offer couples counseling. The man can take advantage of individual services as educational contents

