^a^DREAM: Disease Relief through Excellent and Advanced Means.

These strategies will be implemented according to standard clinical practices in Malawi with some modifications based on the international experiences described in the literature.

The *male champion* is a figure present in a few settings that conducts home visits with men and couples and follows up with men who did not accompany their partners to ANC visits [39]. Usually, this role is covered by the female expert clients, namely HIV-positive patients working in the organization as volunteers after appropriate training. Some men among patients who are receiving treatment will be identified and trained to cover this role [40]. The intervention called *male champion* aims to change the beliefs and attitudes of men, not intervening directly on individuals but upon entire communities and particularly involving community leaders.The *special day* is a practice that is becoming increasingly common to facilitate access to health facilities by vulnerable groups such as adolescents [41,42]. In this study, we target men. The special day takes place with an extraordinary opening of the clinical center once a month on a prefestive day (Saturday). During this day, access will be reserved exclusively for men, including those who are not on treatment for HIV. The center will offer free health promotion services to all participants. This intervention aims to remove the attitude linked to beliefs regarding masculinity, in which the male partners see access to health centers as an activity suitable only for women. The special day aims to make the clinical center more male-friendly and therefore attempts to overcome the social pressure that pushes men to have only sporadic attendance.The intervention based on the use of incentives (*nudge*) [43] to men who follow the prevention and treatment program aims to evaluate whether this action is effective in guiding behavior change toward the test, treatment, involvement, and adherence to therapy approach. The intervention defined as *budget* aims to remove the obstacles of a structural or a material nature, which supports the costs related to transportation to health care facilities and time taken away from work through a noneconomic incentive.

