The educational content will be delivered using 3 different approaches. The *special day* arm will address the community in the catchment area of the clinical center, but the intervention will take place at the facility level. Through visibility activities such as leaflet distributions or information campaigns with audio messages, men living in the communities surrounding the treatment center will be invited to an extraordinary opening day at the center dedicated only to men. During the special day, the center’s clinical staff will offer basic health care services such as HIV testing and counseling, blood pressure measurement and counseling on cardiovascular disease, blood glucose measurement and counseling on diabetes, and nutritional evaluation and counseling. During the morning, group educational activities led by male community health care workers together with the doctors of the center and 2 educational sessions using drama techniques will be conducted. In the *male champions* arm, the intervention will be conducted at the level of regional and religious communities, with group educational sessions and use of the *male champions*. Male champions will be selected from patients receiving treatment for HIV for more than a year at the local DREAM centers. The educational sessions, based on an interactive approach with questions and answers both from the audience and the male champions, will last between 30 min to an hour. The male champion will be allowed to prolong the intervention if the audience requests it. Meetings will be planned and implemented in communities where at least five patients who receive treatment at DREAM centers reside, including religious communities in those regions. In the *nudge* arm, the intervention will be directed to individuals or to male partners of female patients being treated at DREAM centers. Women who agree to participate in the study will be asked to invite their male partners to the center for a health education session, and male partners who agree to participate will receive an incentive in the form of a food package, approximately worth US $8. At the second visit, the couple will be given a health education session based on educational materials prepared for the study.

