## Discussion

### Study Strengths

This study aims to assess interventions targeted at enhancing the involvement of males in women antenatal health care in Malawi. Male involvement in prenatal care is still one of the lowest in the world in Malawi, ranging from 3.2% to 23% [27]. There are multiple reasons for the limited role of male partners in women’s health initiatives. Instead of addressing singular factors supposed to directly cause limited male involvement, the approach of our study is based on an ecological model [17]. The decision to base interventions on a theoretical framework is one of the strengths of this study. In fact, a theory-based approach allows us to better understand the reasons for failure or success of an intervention, develop better strategies, and evaluate their external validity [16,50]. In particular, the ecological model was chosen for this study because it considers not only the beneficiaries (HIV-positive women and their partners) and ART adherence as done in other studies [15] but also the social context that can facilitate or hinder the adoption of healthy practices, namely retention in care and adherence to therapy for HIV PMTCT. All the interventions being evaluated act on individual and interpersonal elements, through couple health education. In addition, each intervention addresses other elements such as the health structure, the community, or the structural level linked to transportation costs. This design allows us to understand how the different levels affect behaviors within the target group and, therefore, health outcomes. Another strength of these interventions is the implementation of these activities in a real-life setting, with the use of personnel already active in the center. This is a significant strength of this study, as it provides reproducible information to other sites.

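### Couples counseling is declared common to all three interventions, but the delivery plan schedules a couple session only in the Nudge arm, so level-specific conclusions are not supported unless a shared base is shown

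*Protocol article*

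**What the plan says.** Strategy of the Study presents individual-level and interpersonal-level activities as running through all three interventions, with each arm adding one further level (community, health system or structural). On the interpersonal level it states that "all interventions will include support activities that are aimed at the family (couples counseling"). Study Strengths says the same: "All the interventions being evaluated act on individual and interpersonal elements, through couple health education".

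The Interventions section then says that the educational content reaches people by three different approaches, and describes each:

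- **Nudge (Kapeni).** Table 1 says that, when the partner comes, "the personnel will give a food package and offer couples counseling". The text adds: "At the second visit, the couple will be given a health education session based on educational materials prepared for the study".
- **Special Day (Balaka).** Table 1 lists basic health services, group education and drama sessions. On access: "During this day, access will be reserved exclusively for men, including those who are not on treatment for HIV".
- **Male Champions (Kapire).** Table 1 lists individual counseling for men, then "Home care for defaulting male patients Sensitization campaigns in local communities", and campaigns in public spaces. The text describes group sessions in regional and religious communities and says that the arm works by "not intervening directly on individuals but upon entire communities". The same section also describes the male champion, as the role exists in a few settings, as visiting men and couples at home, and says that male patients will be trained for it.

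**The concern.** Outcomes and Statistical Methods says that using the same indicators in every arm makes it possible to assess the differential impact of the community, health-system and structural levels. Study Strengths says that the design shows how the different levels affect behavior. Both statements need the three arms to share the individual and interpersonal base and to differ only in the added level.

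If the couple component is in fact delivered mainly or only at Kapeni, a better result there would be credited to the incentive although it also reflects couple education. A poorer result at Balaka would count against the health-system level although that package may have lacked a component it was said to contain. Couple education also lies close to the intermediate outcomes, such as accompaniment by the partner and the partner-involvement score.

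**Working it through.** The article gives no figure on this point to reproduce. The check sets the claim beside the delivery plan, arm by arm.

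| Arm (center) | Couple component claimed? | Couple session in Table 1 or the delivery text? | Nearest monitoring indicator in Textbox 1 |
|---|---|---|---|
| Nudge (Kapeni) | Yes | Yes, in both, when the partner attends | Eligible couples; incentives and counseling sessions |
| Special Day (Balaka) | Yes | No; the described day is closed to women | Men receiving services, including HIV test and counseling |
| Male Champions (Kapire) | Yes | No; but the described role includes home visits with couples | Number, duration and attendance of meetings; qualitative reports |

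**Is Table 1 only a list of each arm's distinctive element?** No. It names individual counseling at Kapire and couples counseling at Kapeni, both of which belong to the supposedly common base. The absence of any couple activity from the other two rows therefore carries some weight.

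**Can monitoring settle it?** Not as listed. Balaka's list counts counseling, but of men on the special day. Kapeni's list counts counseling sessions without calling them couple sessions. Kapire's list counts meetings. No indicator measures couple sessions in the same way across arms.

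**What a between-arm contrast would contain.** Assuming additive effects, for illustration:

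Nudge minus Special Day = (structural minus health-system effect) + (couple-education effect, if absent at Balaka) + (Kapeni minus Balaka center difference).

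The level claim concerns the first term. The second drops out only if the base is shared. The third remains in any case, because there is one center per arm.

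**How many women are concerned.** Preintervention enrollment (Results): Balaka 166, Kapire 75, Kapeni 78.

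- All intervention centers: 166 + 75 + 78 = 319.
- No couple activity described (Balaka): 166 / 319 = 52%.
- Ambiguous (Kapire): 75 / 319 = 23.5%.
- Couple session scheduled when the partner attends (Kapeni): 78 / 319 = 24.5%.
- If Kapire also has none: (166 + 75) / 319 = 241 / 319 = 76%.

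The range is therefore 52% to 76%, depending on how Kapire is read.

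**The case against.** The strongest reply is that the common component is stated once for all arms and repeated in the Discussion, so it need not be repeated in each row of Table 1. Table 1 does assign the individual and interpersonal levels to all three arms. All staff received one guide and one training, with tools built on national couples-counseling standards. The guide is not shown, and an article may leave session detail to it. At Balaka the men-only rule covers one Saturday a month, and couples could be seen at the women's routine visits. Partners are also invited to come with the woman for testing and counseling, and the text does not limit this to one center.

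Much of this stands as a limit on the point. A reader might infer that couples were educated only at Kapeni and that the shared-base claim is false as delivered. The documents do not support that. They contain no delivery data, they state that every arm receives the component, and the male-champion role as described includes couples. The phrase about not acting directly on individuals cannot be read literally either, since Table 1 lists individual counseling in that same arm.

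It does not remove the contradiction. The couples-counseling standards concern content, not delivery to couples. The joint invitation is described for the preintervention phase and for outcome measurement; it shows a route by which couples may attend, not an intervention session. The home-visit sentence is not carried into Table 1, the delivery text or the Kapire indicators. For Balaka, no setting other than the men-only day is described. These are positive statements that disagree, not merely detail left out of an article.

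A second reply is that each arm is already inseparable from its single, nonrandomized center. That is true, and reconciling the couple component will not make the comparison clean. It is nevertheless a separate problem: even with many centers per arm, packages that differ in an undeclared component could not isolate a level. The Limitations section does not mention it.

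**Conclusion.** The point holds as an unreconciled contradiction with a conditional consequence. The article claims a couple component in three of three arms. The listed activities schedule a couple session in one, leave one ambiguous and describe none in the third. If delivery follows Table 1 and the delivery text, a Nudge advantage would combine the incentive with couple education, and the level-specific claims in Outcomes and Statistical Methods and in Study Strengths would not be supported.

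The 52% (Balaka alone) and 76% (with Kapire) describe how many baseline women attend centers without a scheduled couple session. They are not effect sizes, and they rest on preintervention enrollment, which may differ from postintervention enrollment. The conclusion assumes that the listed activities reflect what is delivered; the staff guide could show otherwise. Whether couple sessions actually differed between arms cannot be told from the article.

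**What to change.** 1. Reconcile Strategy of the Study and Study Strengths with Table 1 and the rest of the Interventions section. State for each arm whether couple counseling is delivered, by whom and at which contact.
2. Add one identically defined indicator, the number of couple sessions delivered, to all three lists in Textbox 1.
3. Unless those counts show a shared base, limit the claims in Outcomes and Statistical Methods and in Study Strengths to a comparison of three whole packages, and state that any Nudge effect includes couple education.

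Items 1 and 3 are wording only. Item 2 adds one count at Balaka and Kapire and a sharper definition at Kapeni. The interventions began on August 1, 2020, so sessions held before the count starts may not be recoverable, and the report should say so. None of this asks for a change in what any center delivers. The other cost is a narrower conclusion, and the confounding of arm with center remains.
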